#### Comprehensive geriatric assessment and care

The team conducting the CGA and care intervention in the trial consists of internal medicine physicians with geriatric profiling, study nurses, physiotherapists (and/or occupational therapists) and dieticians. The team works in close contact with the colorectal surgeons at the clinic. During the day of interventions, each patient is individually assessed by one member of each profession (Fig. 1).

The multimodal concept of comprehensive geriatric assessment and care is considered best practice when treating frail elderly patients [30, 37]. The multiprofessional and team-based examinations and assessments of the elderly individual identify both problems and resources in the elderly population and the assessments should lay the grounds for recommended treatment and follow-up. The use of CGA enables underlying unidentified conditions and problems to be identified and, if needed, specifically targeted, optimized and treated [38, 39]. Considering sarcopenia and nutritional problems being highly present amongst the frail elderly, physiotherapists (and/or occupational therapists) and dieticians are important members of the CGA and care team. A geriatric assessment, especially with a focus on medications, including risks of polypharmacy, inappropriate medications and ADRs, is also crucial [30, 40, 41].

### Criteria for discontinuing or modifying allocated interventions {11b}

At the weekly follow-up where every patient currently in the intervention group is discussed, each profession describes the planned intervention and the progress since the last meeting. If indications arise that there are compliance issues or complications (e.g. bowel obstruction, bleeding) requiring more urgent treatment, or when the intervention is deemed not to have any further benefits, the intervention will be terminated, and the patient will proceed to surgery without further delay.

### Strategies to improve adherence to interventions {11c}

There is a limited number of health care professionals working for each profession in the trial, as one way of making the continuity to the study protocol as great as possible. Prior to the study start, the participating health care professionals underwent education in using the instruments and expertise on each assessment tool is available if needed.

The project steering group meets regularly and performs internal monitoring of entered forms and CRFs, to assure compliance with the protocol and to identify eventual errors.

Prior to the weekly follow-up meetings, representants of at least one health care profession participating in the CGA team have contact with the intervention patient in order to evaluate the intervention, e.g. if the patient is using the newly prescribed medications, following the exercise programme, etc.

### Relevant concomitant care permitted or prohibited during the trial {11d}

The inclusion of a patient in the trial does not alter standard protocol—the same investigations, appointments, treatments, etc. will be offered and carried out. The only amendment to standard protocol is the addition of CGA and care, to patients in the intervention group.

### Provisions for post-trial care {30}

There are no provisions for ancillary or post-trial care, and this care will not be any different to the standard protocol for patients included in the study. As in conventional care, patients are insured under the Swedish patient insurance (LÖF) and may be entitled to compensation under the Swedish Patient Injury Act.

### Outcomes {12}

Primary endpoint:All-cause 90-day mortality

Secondary endpoints:Length of hospital stay and the total number of hospital days within 3 months after dischargeDischarge destination (home or nursing facility) and use of home help services30-day readmission ratesADL performance at follow-up in comparison to baselineSafe medication assessment at follow-up in comparison to baseline, adverse drug reactions (ADRs), underuse of evidence-based drug therapy and effects of inappropriate medications (analysed retrospectively)CFS-9 score at follow-up in comparison to baselinePostoperative complications according to the Clavien-Dindo scale at follow-upHealth-related quality of life (HRQoL) at follow-up in comparison to baselineCost-effectiveness based on mortality and HRQoL data (quality-adjusted life years [QALYs]) and costs of hospital care and primary care at baseline, 2 and 12 months post-surgeryAll-cause 1-year mortality

#### Outcomes and measurements

*Hospital stays and discharge destination*, data regarding the length of hospital stay, total number of hospital days within 3 months after discharge, discharge destination and use of home help services and 30-day readmission rates for all participants is collected from patient medical records.*Dependence*, evaluation of the level of independence/dependence in an elderly individual is of great importance for example when establishing the need of home help services or other assistance. This is assessed using the activities of daily living (ADL)-staircase, which is a validated and commonly used instrument. The screening results in a score from 0 to 9, where 0 is completely independent and 9 is completely dependent [42, 43]. A clinically significant change is defined as a change of minimum 1 step in any direction on the ADL-staircase. ADL-function is assessed at baseline and at post-op visit (approximately 2 months post-surgery). The patients are assessed by a physiotherapist or a study nurse at baseline and follow-up.*Physical function*, the physiotherapists are also using hand grip strength (HGS) and six-minute walk test (6MWT) to make an overall assessment of the patient’s physical status to establish individual recommendations on physical activity and exercise. Both HGS and 6MWT have previously been used in assessments of frail elderly patients [44, 45]. The tests are performed at baseline and not at follow-up and are only conducted on patients in the intervention group as part of the CGA and care intervention.*Nutrition*, malnutrition is common in the elderly population, especially if hospitalized, living in nursing facility or having home help services. Malnutrition is often unrecognized if not specifically targeted. The Mini-Nutritional Assessment-Short Form (MNA-SF) is a validated instrument for nutritional screening in frail elderly individuals. It renders a score which places the patients in one of three groups: normal nutritional status, at risk of malnutrition or malnourished [46, 47]. A clinically significant change is defined as a change in group classification. The patients in the intervention group are screened by a dietician at baseline and by a ward nurse or a dietician at the day of/day before surgery. The patients in the control group are screened by a study nurse at both measurements.*Medication safety*, polypharmacy and the use of potentially inappropriate medications is a growing issue in the elderly population. There is often a need of reviewing and altering an elderly individual’s prescribed medications to reduce the risk of adverse drug reactions and to enable beneficial pharmacological treatments [48–50]. The Safe Medication Assessment (SMA), including a review of the current list of medications [51], is used as a basis for assessing the individual patient’s medications in the trial. The instrument renders a score of 0–30, where a higher score indicates a safer treatment. A clinically significant change is defined as a shift of minimum 1 point in either direction. The questionnaire is filled out by a study nurse at baseline and at revisit, for all participants. To identify adverse drug reactions (ADRs), underuse of evidence-based drug therapy and effects of inappropriate medications, scoring scales [49, 50] and clinical judgements based on medical records will be used. These judgements will be retrospectively performed by senior clinicians [52].*Cognition*, a decline in cognitive function is naturally present in the ageing process. Some elderly individuals are experiencing a more pronounced decline, resulting in cognitive impairment or dementia [53]. In the trial, the Mini-Mental State Examination (MMSE) is used as a screening instrument of cognitive function at baseline. It is a validated and reliable assessment tool in screening for cognitive impairment [54]. The screening is performed by a study nurse at baseline for all participants, but the measurement is not done at follow-up.*Frailty* is an independent risk factor of adverse health outcomes and death [21] and also a predictor of increased hospital and health care costs [25]. The degree of frailty is assessed using the Clinical Frailty Scale (CFS-9). The scale ranges from 1, “very fit”, to 9, “terminally ill”. The scale has been validated and proven to be of prognostic value in clinical practice [26, 55, 56]. The estimates are performed by a study nurse at baseline and at revisit, for all participants. A clinically relevant change is defined as a shift of minimum 1 step on the scale. During the initial phase of the trial’s recruitment, a revision of the CFS-9 scale was made, including minor adjustments in the description of the different levels of frailty [57]. Before the updated version (v 2.0) was put into use, a new application to the Swedish Ethical Review Authority was made and was approved on 2021-05-31.*Complications*, postoperative complications are common in elderly patients undergoing colorectal cancer surgery. The complications can result in additional treatments, reoperations, the need of intensive care and death [7, 8]. The Clavien-Dindo classification is a validated and clinically relevant instrument for identifying and grading adverse postoperative events [58]. The postoperative complications are assessed by a physician based on data from the medical records at the time of revisit, for all participants.*Comorbidity*, the patient’s comorbidity is valued through the Charlson comorbidity index (CCI). The instrument is used to assess the total burden of disease and predicts a 10-year mortality for a patient, by using 19 categories of comorbidities. Each condition is given a grade of 1, 2, 3 or 6, based on the risk of death associated with the specific comorbidity [59, 60]. The CCI index estimate will be performed by a physician, based on data from the medical records at baseline and at revisit, for all participants.*Health-related quality of life (HRQoL)*. The instrument EuroQoL-5D-5L (EQ-5D-5L) is used to assess HRQoL in the trial. The tool consists of a questionnaire containing five health dimensions with five response levels and of a visual analogue scale (VAS) where the patient estimates their own overall current health. Each estimated score is represented by an index value which is derived from a pre-defined value set [61, 62]. The assessments are overseen by a study nurse at baseline and at follow-up (2 and 12 months), for all participants.*Health economical calculations*. A health care system perspective will be applied including hospital and primary care. Cost-effectiveness will be analysed based on mortality and HRQoL data (quality-adjusted life years [QALYs]) and costs of hospital care and primary care at baseline, 2 and 12 months post-surgery. An incremental cost-effectiveness ratio (ICER) is calculated regarding cost/QALY gained. QALYs are calculated by multiplying the health state value with the patient’s survival time at 12 months; see also the “Statistical methods for primary and secondary outcomes” section. Data regarding health care costs will be collected and documented for all participants at 2 months and 12 months from baseline. Hospital costs will be obtained from the Swedish Cost-per-Patient database [63] and from hospital-specific administrative systems. Primary health care costs will be collected from the administrative regional health care database in Västra Götalandregion (VEGA) [64] and by the use of models and actual health care contacts.*Mortality*, mortality data will be extracted from patient medical records and cross-checked against the Swedish Population Registry regarding all participants at 2, 3 and 12 months from baseline.

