**Fig. 1 Fig1:**
[figure not shown]
Description of the CGA and care concept in the study

**Table 1 Tab1:** Screening instruments and assessments used for the intervention group, at baseline, at post-op visit (approximately 2 months post-op) and at 12 months post-op

Health care professional	Outcome and instruments	Other evaluations	Time of measurements
Internal medicine physician	- **Comorbidity**—*Charlson comorbidity index (CCI)* - **Medication safety**	- Review of SMA and current medications - Overall assessment of physiological status (including blood pressure and ECG)	**CCI** - Baseline - Post-op visit
Study nurse	- **Frailty**—*CFS-9* - **HRQoL**—*EQ-5D-5L* - **Cognition**—*MMSE* - **Medication safety**—*SMA and list of medications* -** Complications**—*Clavien-Dindo scale*		**CFS-9** - Baseline - Post-op visit **EQ-5D-5L** - Baseline - Post-op visit - 12 months post-op **MMSE** - Baseline **SMA** and list of medications - Baseline - Post-op visit **ADL** - Post-op visit **Complications** - Post-op visit
Physiotherapist	- **Dependence**—*ADL-step* - **Physical function** *hand grip strength (HGS) and six-minute walk test (6MWT)*	Overall assessment of the physical status	**ADL** - Baseline **HGS** - Baseline **6MWT** - Baseline
Dietician	- **Nutrition**—*MNA-SF*	Overall assessment of the nutritional status	**MNA-SF** - Baseline - Day of/day before surgery

All patients in the intervention group are discussed weekly in a group consisting of at least one representative from each profession. During these weekly meetings, the expected benefit of the interventions is weighed against the risk of delaying the surgery in each individual case. Adherence to the individually prescribed recommendations is evaluated and when the intervention is completed, or the patient for any given reason is not able to follow the recommendations, the intervention is terminated. To allow the CGA and care intervention to reach as much effect as possible, we have argued the need of, in some cases, allowing the time from diagnosis to surgery to be somewhat prolonged. In general, that time frame is 2–6 weeks but may in the trial setting be extended for up to 8 weeks. The overall objective is though, as in conventional care, to prepare the patient as quickly as possible for surgery without taking unnecessary medical risks. The postoperative phase is similar in both groups (Fig. 1).

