## Assignment of interventions: blinding

### Who will be blinded {17a}

Neither participants nor caregivers are blinded to group assignment, as the intervention will be apparent. However, results will be analysed without knowledge of details of the groups.

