### Data management {19}

Each participant will be dealt a study number which further is used for identification. A specific key file is created for the identification, where personal identity numbers and study numbers are stored. This key file will only be kept at a hospital computer belonging to the local principal investigator. All examination results and medical considerations are documented in the medical chart. This is protected by the Swedish Law of Secrecy and Public Access. A CRF for each patient and all entered screening instruments (Tables 1 and 2) are obtained and held in a project-specific database and in patient-specific study binders.

There is no double data entry. Members of the steering committee intermittently conduct internal monitoring where the quality of entered study data is assessed. Likewise, an assessment of adherence to the protocol is conducted during these meetings. Adherence to the individual recommendations made by the health care professionals during the intervention is assessed during the weekly follow-up meetings (see item 11c).

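### Adverse drug reactions, and to a lesser degree underuse and inappropriate medication, are judged by unmasked clinicians from charts that hold a physician medication review in the intervention arm only

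*Protocol article*

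**What the plan says.** The Outcomes {12} section lists, within the medication endpoint, "adverse drug reactions (ADRs), underuse of evidence-based drug therapy and effects of inappropriate medications (analysed retrospectively". Under Outcomes and measurements, Medication safety, the method is that "scoring scales [49, 50] and clinical judgements based on medical records will be used", and "These judgements will be retrospectively performed by senior clinicians".

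Table 1 (intervention group) gives the internal medicine physician a "Review of SMA and current medications". Table 2 (control group) lists a nurse-completed SMA and medication list, and no physician medication review. The section on comprehensive geriatric assessment and care gives the rationale: "A geriatric assessment, especially with a focus on medications, including risks of polypharmacy, inappropriate medications and ADRs, is also crucial".

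Data management {19} states, for all participants, that "All examination results and medical considerations are documented in the medical chart".

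On masking, section 17a leaves participants and caregivers unblinded and adds: "However, results will be analysed without knowledge of details of the groups". Section 17b then says that the trial has no blinding.

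**The concern.** The intervention adds to the data source of its own outcome. A physician looks at the drug list of every intervention patient and the findings enter the chart. Senior clinicians later read charts to decide whether an ADR, an omission or a harmful drug was present. No equivalent entry is planned for controls.

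Two problems follow. First, an event that happens equally often in both arms may be recorded more often where someone was asked to look for it. Second, notes from the intervention day tell the reader which arm the patient was in, and these items call for clinical judgement. A reader who knows the allocation may treat a drug choice more leniently because a review of it is documented.

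At stake is whether a difference between arms, or the absence of one, can be read as an effect on drug safety. Unequal ascertainment arises when the data are collected, and no later adjustment removes it.

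**Working it through.** **The plan's own figures.** The document gives no event rate, detection rate or power for this endpoint. The sample size of 170 per arm is for 90-day mortality and is not in question here.

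**The chain of statements**

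| Step | Intervention arm | Control arm | Where |
|---|---|---|---|
| SMA and medication list by a nurse | baseline and post-op visit | baseline and post-op visit | Tables 1 and 2; Outcomes and measurements |
| Physician review of SMA and drugs | yes | not listed | Table 1 against Table 2 |
| Surgeon and pre-anaesthetic visits, visit at about 2 months | yes | yes | Standard protocol |
| Findings written in the chart | yes | yes, but no medication review to write up | Data management {19} |
| Masking of the judging clinicians | none stated | none stated | 17a, 17b |

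The preoperative period also differs. The intervention group is assessed on a weekly intervention day and may have up to 8 weeks before surgery. Controls are measured at admission. No common period for counting ADRs is given, so an open chart search could cover a longer and more closely observed preoperative period in the intervention arm.

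**Illustration (assumed values; none comes from the document).** Let p be the true ADR risk, equal in both arms, and let s_C and s_I be the share of ADRs that the chart reveals in the control and intervention arms.

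Observed risk ratio = (p × s_I) / (p × s_C) = s_I / s_C, whatever the value of p. With s_C = 0.60:

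- s_I = 0.65: 0.65 / 0.60 = 1.08
- s_I = 0.70: 0.70 / 0.60 = 1.17
- s_I = 0.80: 0.80 / 0.60 = 1.33
- s_I = 0.90: 0.90 / 0.60 = 1.50

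A real benefit can be hidden in the same way. With a true risk ratio of 0.75 and detection of 60% against 80%, the observed ratio is 0.75 × 0.80 / 0.60 = 1.00.

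**Chance of a false result of more ADRs with CGA.** Take 161 evaluable patients per arm (170 × 0.95 = 161.5, rounded down) and a two-sided 5% test of two proportions. The probability is Φ[(d − 1.96 × SE0) / SE1], where d is the observed difference, SE0 the pooled and SE1 the unpooled standard error. For p = 0.20 and s_I = 0.80, the observed rates are 12% and 16%:

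- SE0 = √(0.14 × 0.86 × 2/161) = 0.0387
- SE1 = √((0.12 × 0.88 + 0.16 × 0.84)/161) = 0.0386
- (0.04 − 1.96 × 0.0387) / 0.0386 = −0.93, so the probability is about 0.18

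| True risk p | s_I 0.65 | s_I 0.70 | s_I 0.80 | s_I 0.90 |
|---|---|---|---|---|
| 10% | 4% | 6% | 10% | 17% |
| 20% | 5% | 8% | 18% | 32% |
| 30% | 5% | 10% | 26% | 49% |
| 40% | 6% | 13% | 36% | 65% |

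The nominal value in that direction is 2.5%. The table covers unequal detection only. It does not include the effect of a judge who knows the arm, which could act the other way and for which the document gives no basis for a number.

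**The case against.** The control chart is not empty. Every patient has a further surgeon appointment, a pre-anaesthetic assessment, referrals where needed and a visit at about 2 months. The nurse SMA, the medication list and a physician-rated comorbidity index are collected for all participants, and the article describes the postoperative phase as similar in the two groups. This stands. It narrows the difference between charts but does not close it, because the physician medication review remains in one arm only.

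The three components are not equally exposed. Underuse and inappropriate drugs can be judged largely from diagnoses and drug lists, which exist in both arms, and scoring scales may standardise part of the judgement. This also stands: the problem is clearest for ADRs.

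The passage on the focus of a geriatric assessment is general rationale and does not say what is charted. The contact before weekly meetings in section 11c is an adherence check. Neither proves that more ADRs are recorded. The case rests on Table 1, Table 2 and the charting statement.

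The full protocol may mask these judges. One could also read the masking of analysis in 17a as reaching an endpoint that is described as analysed retrospectively. That reading is weak, since 17b says there is no blinding and the judgements produce the data that are later analysed. The article itself fixes the source, the judges and the timing, so the point is not mere silence.

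A reader might infer that CGA will appear to cause more ADRs. The document does not support a fixed direction: more documentation can raise the count, while known allocation or a recorded rationale can lower it.

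**Conclusion.** The concern holds for part of one secondary endpoint. Followed as written, the plan gives judgements by clinicians who are not masked, from records that differ by arm on the topic being measured. This bears most on ADRs and less on underuse and effects of inappropriate medication.

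The size cannot be computed from the document. The spurious risk ratio of 1.08 to 1.50 rests on equal true risk, 60% detection in controls and 65% to 90% in the intervention arm, all of them assumptions.

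A reader might go further and conclude that the endpoint can say nothing about whether CGA makes drug treatment safer. That is too strong. The SMA score belongs to the same endpoint, is collected by a nurse from all participants and does not depend on the chart judgement. Ninety-day mortality, taken from medical records and checked against the population registry, is not affected either. The correction is worth making because it is cheap and, as the judgements are retrospective, it can still be applied alike to every participant.

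**What to change.** Under Medication safety, state the following.

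1. **Main analysis.** The senior clinicians already planned judge masked to arm, from an extract of records available in both arms: medication lists, SMA, diagnoses, and surgical-admission, discharge, readmission and post-op visit records. CGA notes and all mentions of CGA are removed.
2. **Window.** ADRs are counted over one period common to both arms, from surgical admission to the post-op visit. The baseline lists are taken at different times in the two arms (the intervention day, or hospital admission), which is a further reason to start the count at admission.
3. **Stopped drugs.** Where a drug was stopped, the extract gives the reason in neutral wording that does not reveal the arm. Otherwise justified deprescribing could be scored as underuse, mainly in the intervention arm.
4. **Supplementary analysis.** ADRs from randomisation onward are reported using all records, so that preoperative reactions to newly prescribed drugs are not lost. The report says that this analysis carries the unequal documentation described above.
5. **Limitation.** The report acknowledges that changes in the drug lists may still partly reveal the arm.

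The cost is a change of wording and some staff time to prepare the extracts. ADRs recorded only in CGA notes would appear only in the supplementary analysis. No treatment, visit or measurement changes.
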